Persons who are in the intervention group or the wait control group whose depressive symptoms worsen (but not to the point of ineligibility) would first be evaluated by the counselor in conjunction with the study's clinical team and with the CCT medical monitor. Based on this assessment, a decision could be made to continue CBI treatment alone or the client could be provided referral to standard of care treatment possibly including non-specific counseling. This treatment would be recorded in the client monitoring records.

We should note that some of the counselors who will deliver the CBI intervention are also qualified to provide other services (for example, some of the Mae Tao Clinic counselors providing the intervention also work at the Counseling Center on a part-time basis). We will ask for the period of the intervention, that the CBI counselors provide only CBI to their study clients. If referrals are made for other services (or clients independently seek other services including,

possibly, non specific counseling) these other services would be provided by someone other than the CBI counselor.

|                                                               | Month |    |    |    |    |    |    |    |    |    |    |    |
|---------------------------------------------------------------|-------|----|----|----|----|----|----|----|----|----|----|----|
|                                                               | 1     | 2  | 3  | 4  | 5  | 6  | 7  | 8  | 9  | 10 | 11 | 12 |
| 1. Training on CBI Method                                     | XX    | XX |    |    |    |    |    |    |    |    |    |    |
| 2. Practicum Round on CBI                                     |       |    | XX | XX | XX |    |    |    |    |    |    |    |
| 3. Recruitment                                                |       |    |    | XX | XX |    |    |    |    |    |    |    |
| 4. Screening and Baseline Interviews of Case and Wait-Control |       |    |    |    | XX | XX |    |    |    |    |    |    |
| 5. Intervention (Case Group)                                  |       |    |    |    |    | XX | XX | XX | XX | XX |    |    |
| 6. Follow-up Interviews (Case and Wait-Control Groups)        |       |    |    |    |    |    |    |    |    | XX |    |    |
| 7. Intervention for Wait-Control Group                        |       |    |    |    |    |    |    |    |    | XX | XX | XX |

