| 8. Study Wrap-up                                              |       |    |    |    |    |    |    |    |    |    | XX | XX |

*Follow-up interviews.* All follow-up interviews (including with the wait-control group) will be conducted at the end of the intervention for the case group, which would be no more than 3 to 4 months after the date of enrollment into the study.

Following completion of the trial, the data will be analyzed, and if the intervention is found to be effective, it will become part of the services provided by the counselors to torture and violence survivors.

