### 5) *A brief data analysis plan and description of the nature of the variables to be derived*

As noted previously, depression and trauma were the two mental health problems that were prominently identified in the qualitative research (IRB#3047) that preceded this intervention evaluation phase of the project. Depression symptoms will be measured using a modified, locally validated version of the Hopkins Symptoms Checklist (HSCL) and trauma exposure and symptoms will be measured using a modified, locally validated version of the Harvard Trauma Questionnaire (HTQ). The data generated from the validation study has been used to develop depression and trauma scale cutoff scores for the study population. The counselors will calculate the total score for these subscales during the initial screening interview, since scores on either of these scales above the cutoffs are part of the eligibility criteria (13 or above for

depression symptoms and 45 or above for trauma symptoms). Following randomization into a case group and a wait-control group, the counselors will provide the intervention to the case group. At the end of the intervention, the case group and the wait-control group will be re-interviewed using the same instrument employed in the screening interview. The mean change in the various subscales between pre and post intervention interviews will be calculated and subtracted from the mean change (calculated in the same way) for the wait-control group. The differences will be the amount of change on each scale due to the intervention.

In terms of statistical analysis, we will keep the data on study participants in the intervention group who get other standard of care treatment or participants in the wait-control group who need immediate treatment. All study participants who meet screening criteria for eligibility and enroll in the study will be included in the analysis on an intent to treat basis.

6) *If human biospecimens (blood, urine, saliva, etc.) will be collected, provide details about collection, volume (ml) or number, use, storage, identification, and disposal.*

Not Applicable

7) *Describe how subjects will be screened for eligibility and assigned to study/intervention and comparison/control groups.*

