At the end of the study those counselors providing interventions found to be effective will continue to provide treatment, both to those currently receiving the treatment and to new clients. Persons who have not yet received the new intervention will be eligible to receive it regardless of whether they had previously received any treatments. If a subject's participation ends prematurely for whatever reason, they could continue to work with a clinician or other care services as needed.

Any participant who does not come to a regularly scheduled session will be followed up by the counselor to determine whether they are a formal withdrawal or if there is some other barrier that can be overcome to continue treatment. If the participant does not want to participate further, the counselor or project staff will try to find out the reason for withdrawal. Otherwise, no further action will be taken. Our sample size calculations are based on an assumption that about 25% of participants will choose to withdraw from the study and from treatment.

*13) Describe the process for referring subjects to care outside the study, if needed.*

One local counterpart, Mae Tao Clinic, operates a primary care clinic with a Counseling Center and with referrals to Mae Sot Hospital, a Thai hospital in Mae Sot with limited in-patient psychiatric services. Clinical supervisors for the CBI intervention will be in weekly contact with JHU and consulting CBI experts on a routine basis and will communicate with them on an as needed basis. Persons who are found at screening or during the study to be in active danger of harming themselves or others will be immediately discussed with clinical supervisors and the safety response team for referral to the nearest and most appropriate treatment site.

*14) For studies that evaluate interventions, have a randomized study design, and/or are a clinical trial, provide power calculations for projected sample size.*

To calculate sample size, we relied on a pair-wise comparison – that is comparing the intervention to the wait-control condition. We calculated sample size and power calculations using effect size analyses of depression and trauma symptom scores. We estimated that to find a moderate effect size (.50) for either depression or trauma, we would need 120 participants in each arm. We used power=0.80, alpha=0.05, a design effect of 1.5, a drop-out rate of 25%, and a 1:1 ratio of intervention (case) to wait-control.

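### The protocol treats stopping CBI as leaving the study and plans no outcome interview for those who stop, which can lose outcomes mainly in the case arm despite the intent-to-treat promise; its follow-up limit also contradicts its schedule table.

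*Protocol*

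**What the plan says.** All references are to the Protocol.

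- **Section 4, item 12 (end of participation).** A missed session leads the counselor to contact the participant and find out whether this is a formal withdrawal or a barrier that can be overcome. If the person does not want to go on, staff try to learn the reason. Then: "Otherwise, no further action will be taken". The item adds the planning assumption that "about 25% of participants will choose to withdraw from the study and from treatment".
- **Section 4, item 5 (analysis plan).** Everyone eligible and enrolled "will be included in the analysis on an intent to treat basis". The effect is the difference between arms in mean change from the first to the second interview.
- **Section 4, item 2 (follow-up interviews).** Both arms are interviewed at the end of the case group's intervention, "which would be no more than 3 to 4 months after the date of enrollment into the study". In the schedule table, screening and baseline interviews occupy Months 5 and 6. The row headed "6. Follow-up Interviews (Case and Wait-Control Groups" is marked in Month 10 only. The same item equates June 2011 with Month 5.
- **Section 7a (consent).** Not attending the first session removes a person from the study. Under the randomisation process in Section 4, item 7, the assignment has been opened and disclosed by then.
- **Section 4, item 10.** Wait-control participants receive CBI after their reassessment, or earlier if their symptoms become clinically significantly worse.

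**The concern.** Stopping therapy and refusing to be measured are different events. Item 12 handles them as one: the trigger is a missed therapy session, and the result is departure from both treatment and study. A person who has had enough of CBI but would sit for a one-hour interview is not provided for.

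The intent-to-treat promise depends on that interview, because a change score cannot be formed without it. An analysis plan can model missing outcomes, but it cannot recover interviews that nobody attempted.

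Two features make the loss potentially unequal between arms. Regular sessions during the comparison period belong almost entirely to the case arm, so the missed-session route operates mainly there. The first-session rule in Section 7a works the same way: a case client can be removed before any outcome is taken, whereas a control would ordinarily reach a first session only after the outcome interview. If those who stop differ in outcome from those who stay, the randomised comparison is distorted.

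The timing conflict is a separate matter. Staff cannot satisfy both the limit counted from enrolment and the schedule table.

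**Working it through.** **1. The plan's own sample size (Section 4, item 14).** Inputs: "to find a moderate effect size (.50) for either depression or trauma, we would need 120 participants in each arm", and "We used power=0.80, alpha=0.05, a design effect of 1.5, a drop-out rate of 25" per cent, with 1:1 allocation. Two-sided alpha is assumed, since sidedness is not stated.

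- Base size per arm: 2 × ((1.960 + 0.842) / 0.50)² = 62.8, so 63, or 64 by the t-test.
- Design effect: 64 × 1.5 = 96.
- Drop-out: 96 × 1.25 = 120, the stated figure. Dividing by 0.75 instead gives 128. The recruitment target of 150 per arm covers either.

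**2. Expected loss at the recruited size.** 0.25 × 150 = 37.5 per arm, or 75 of 300. This leaves 112.5 per arm.

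**3. Power after that loss.** Effective n = 112.5 / 1.5 = 75 per arm. Power = Φ(0.50 / √(2/75) − 1.960) = Φ(3.062 − 1.960) = Φ(1.102) = 86.5%. With all 150 interviewed, effective n = 100 and power = Φ(3.536 − 1.960) = 94.2%. Power is therefore not the problem.

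**4. Possible bias.** Let p be the share of case clients with no outcome and d the difference in mean outcome, in SD units, between those observed and those missing. The all-randomised mean differs from the observed mean by p × d. The 25% is the protocol's figure; d is an assumption, because the protocol gives none.

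| d (assumed) | Shift at p = 0.25 | Share of 0.50 target |
|---|---|---|
| 0 | 0 | 0% |
| 0.3 | 0.075 SD | 15% |
| 0.5 | 0.125 SD | 25% |

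If people stop because they have recovered, the sign reverses. If the control arm loses a share q with difference d′, the net bias is p × d − q × d′, which is zero when the two losses match. The table therefore describes loss confined to the case arm.

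**5. The estimate with everyone interviewed.** If the 25% who stop gain nothing (assumption) and the rest gain 0.50 SD, the all-randomised effect is 0.75 × 0.50 = 0.375 SD. With 150 per arm interviewed, power at that effect is Φ(0.375 / √(2/100) − 1.960) = Φ(0.692), about 76%.

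**6. Timing.** June 2011 is Month 5, so enrolment runs through June and July and Month 10 is November.

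- Shortest interval: 31 July to 1 November, 93 days, about 3.1 months.
- Longest interval: 1 June to 30 November, 182 days, about 6.0 months.
- Latest June enrolment to earliest interview: 30 June to 1 November, 124 days, about 4.1 months.

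On the table's dates, every June enrollee is interviewed later than four months after enrolment.

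**The case against.** The strongest reply is that the protocol never makes the interview depend on finishing therapy. Item 2 sets one group-level time point for both arms, items 5 and 7a say both groups are re-interviewed, and item 11 labels fewer than six sessions a treatment failure without removing those people from follow-up. That stands. A reader might infer that follow-up is tied to completing CBI and that the analysis becomes completers only; the text does not support either. Someone who attended three sessions and has not withdrawn is still due an interview.

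Item 12 also comes after an effort to overcome barriers, and it concerns people who do not want to go on. Some of them would refuse an interview too. That stands, but the item does not ask which of the two they are refusing.

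The loss is not confined to one arm: worsening controls may receive CBI early, the 25% is stated for participants in general, and item 14 mentions people moving away. So it falls mainly, not only, in the case arm. The size of any bias rests on an assumed difference, and its direction is unknown.

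On timing, a reader might infer that follow-up intervals differ between arms. No such plan is stated: allocation is concurrent within counselor and both arms share the interview window. The 3.1 to 6.0 range also uses the outer corners of a table drawn in whole months. Even so, the June enrollees exceed the limit whichever day is chosen.

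Methods for missing data may sit in an analysis plan that is not shown, so their absence here is not a finding.

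**Conclusion.** The concern holds in limited form. The protocol merges stopping CBI with leaving the study, provides no outcome interview for those who stop, and still promises an intent-to-treat change-score analysis. Section 7a contradicts that promise more directly, by removing people after their assignment is known. Followed as written, these rules can lose outcomes unequally between arms.

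The size is uncertain. The shift is 0 to 0.125 SD if 25% of case clients lack an outcome, their outcomes differ from the rest by 0 to 0.5 SD, and control losses do not offset this. The 25% is a planning assumption, not a forecast that a quarter will certainly have no outcome. Power at 0.50 SD remains about 86% with 25% loss in both arms.

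It would go too far to say that intent to treat cannot be delivered. Participants can be kept in their randomised arms with missing outcomes modelled, but the result would then rest on assumptions that the data cannot test.

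The contradiction between the follow-up limit and the schedule table is real and separate. It is a scheduling inconsistency and not evidence of bias between arms.

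**What to change.** 1. In Section 4, item 12, define stopping CBI and declining the follow-up interview as two separate events, recorded separately.
2. Invite every randomised person to the outcome interview, whatever the number of sessions attended, in one window counted from randomisation and identical in both arms. Only refusal of the interview or withdrawal of consent ends follow-up.
3. Reconcile item 12 and the first-session rule in Section 7a with the intent-to-treat statement in item 5, and align the consent wording.
4. Reconcile the follow-up limit in item 2 with the Month 10 entry in the schedule table.

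The cost is revised wording and some extra tracing. Counselors already hold their clients' contact details (Section 5c), and local transport is already reimbursed (Section 8c). Some people will still refuse, so the loss is reduced, not removed. Including people who stopped may also lower the estimated effect, as step 5 of the working shows, but that is the all-randomised effect the protocol says it will report.

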Starting in June 2011, the counselors trained in CBI will begin to implement this intervention with the clients that come to see them as part of the ongoing services provided by AAPP, SAW, and MTC. A practicum round of the CBI intervention began shortly following the CBI training in order to be sure that counselors and supervisors are properly trained in the intervention. The research study will begin in June 2011 when approximately 400 people will be screened into the intervention (for a final sample of 300); approximately half of these would be randomly assigned to the “case” group, to begin the intervention immediately after screening while the other half would be assigned to the “wait-control” group to receive CBI after the “case” group has completed the CBI intervention.

The proposed study will be embedded within the ongoing MTC, SAW and AAPP programs which could include non-specific counseling services, social services and support and, in the case of Mae Tao clinic, medical assistance. That is, we are proposing to study the effectiveness of these intervention strategies in a subset of the clients the organizations serve. The organizations will continue to provide services, as space allows, to anyone who seeks their services regardless of whether they meet eligibility for our proposed study. However, those who meet our inclusion criteria will be invited to participate in the research component of the service program.

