Based on our experience of both client and counselor drop-out and other challenges (i.e. people moving), we chose to inflate the recruitment sample size needed for each arm to 150, resulting in 300 participants. Given the rates of depression and trauma symptomatology found during the previous validity study, we estimate needing to screen approximately 400 torture survivors to identify 300 eligible and willing participants.

15) Describe any plan for reporting test results to participants.

After the intake interview is complete, the counselors will review the results of the depression symptoms subscale (Questions 3.1 – 3.17 in the screening/assessment instrument) and the trauma symptoms subscale (Questions 4.1 – 4.30) and will share these with the client. Data from the other scales will not be available to the clients at the time of the intake screening.

At the completion of the study, all study participants, including wait-controls at that time, will be told what the general results were and informed as to their options for receiving continuing or alternative forms of treatment.

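### The stated requirement of 120 per arm does not follow from its own inputs, which give 128 (126 by normal approximation); the recruitment target of 150 per arm still covers it

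*Protocol*

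**What the plan says.** Protocol section 4, item 14, bases the sample size on a comparison of the intervention arm with the wait-control arm and states that "to find a moderate effect size (.50) for either depression or trauma, we would need 120 participants in each arm". The inputs given there are "power=0.80, alpha=0.05", "a design effect of 1.5", a drop-out rate of 25% and 1:1 allocation. Whether alpha is one- or two-sided is not stated, and no formula is shown.

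Item 12 of the same section says what the drop-out rate refers to: the calculation assumes that "about 25% of participants will choose to withdraw from the study and from treatment". The 25% is therefore a share of those who enter the study.

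Item 14 then adds a further margin, for client and counselor drop-out and for people moving away: "we chose to inflate the recruitment sample size needed for each arm to 150, resulting in 300 participants". Section 2 gives the same total when it says that about 400 people will be screened, "for a final sample of 300".

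**The concern.** The Protocol prints a required number and the inputs behind it, so the number can be checked, and it does not come out. If a quarter of those recruited are lost, the number recruited must be the number needed at the end divided by 0.75. Multiplying by 1.25 gives a smaller figure and leaves too few: 1.25 × 0.75 = 0.9375, so about 6% fewer than needed remain.

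What is at stake is the meaning of the 120. It reads as the enrolment at which the trial still has 80% power. If recruitment fell short of 150, the team could take 120 per arm as sufficient, when on the stated inputs the floor is 126 to 128.

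**Working it through.** **Inputs** (Protocol section 4, items 12 and 14): standardised difference 0.50; power 0.80; alpha 0.05; design effect 1.5; 25% of participants lost; 1:1 allocation; recruitment target 150 per arm.

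**Assumptions added here:** alpha is two-sided, and the design effect stays at 1.5 after drop-out.

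**Step 1. Base size per arm.**
- Normal approximation: n = 2 × ((1.960 + 0.842)/0.50)² = 62.8, so 63.
- t-test: n = 63.8, so 64.

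**Step 2. Design effect.** 64 × 1.5 = 96 evaluable per arm (63 × 1.5 = 94.5 by normal approximation).

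**Step 3. Reproduce the stated figure.** 96 × 1.25 = 120.0, an exact match. Other routes do not reach 120:

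| Route | Per arm |
|---|---|
| Two-sided, no drop-out | 95 to 96 |
| Two-sided, × 1.25 | 118 to 120 |
| Two-sided, / 0.75 | 126 to 128 |
| One-sided, × 1.25 | 93 to 97 |
| One-sided, / 0.75 | 99 to 103 |

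**Step 4. Enrolment that matches the stated inputs.** 96/0.75 = 128 per arm, 256 in total. By normal approximation, 94.5/0.75 = 126 per arm, 252 in total. The stated 120 is 8 short of 128 (8/128 = 6.3%) or 6 short of 126 (6/126 = 4.8%).

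**Step 5. Power if 120 per arm were recruited.** 120 × 0.75 = 90 evaluable; 90/1.5 = 60 effective per arm. Power is 77.5% by t-test and 78.2% by normal approximation.

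**Step 6. Power at the actual target.** 150 × 0.75 = 112.5 evaluable per arm (225 in total with follow-up data); 112.5/1.5 = 75 effective per arm. Power is 86.0% by t-test and 86.5% by normal approximation.

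**Step 7. Loss that the target can absorb.** With 96 evaluable needed per arm, 80% power holds up to a loss of 1 − 96/150 = 36%.

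**The case against.** **The 120 is an intermediate figure.** The trial recruits 150 per arm, above the corrected 128, so the 77.5% describes a trial that nobody plans to run. This stands, and it limits the point to the stated requirement. A reader might infer from the 77.5% that the trial is underpowered; the recruitment target in item 14 shows that it is not.

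**The result is conditional.** Sidedness is not stated, the inflation formula is inferred from a numerical match, and a design effect normally depends on cluster size, which shrinks with drop-out. As an illustration resting on assumptions that the Protocol does not state, suppose that 1.5 applies to enrolled clusters of 240/20 = 12 per counselor. The implied intraclass correlation is 0.5/11 = 0.045. After 25% loss, 9 remain per counselor, the design effect is 1 + 8 × 0.045 = 1.36, the effective size is 90/1.36 = 66 per arm, and power is about 81%. So 120 can be defended on one reading of the design effect. Nothing in the Protocol indicates that this reading was used: it gives one flat value of 1.5, and 120 comes out exactly with that value and × 1.25. The assumptions belong beside the result, but they do not remove the discrepancy on the inputs as printed.

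**Stronger readings that the Protocol does not support:**
- *Drop-out counted twice, or a reserve overstated.* The step to 150 is openly described as a choice made from experience. It also covers counselor loss, which the 25% participant withdrawal does not, and no size of reserve is claimed.
- *A contradiction in section 2.* "for a final sample of 300" follows the number to be screened and precedes the assignment to groups. It reads naturally as the number enrolled, in line with item 14.
- *Only 225 analysed.* Section 4, item 5 plans an intent-to-treat analysis of everyone eligible who enrols. The 225 is the number expected to have follow-up data, not the analysis population.

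**Conclusion.** The point holds as an error in a stated figure. With two-sided alpha and a design effect fixed at 1.5, the printed inputs require 96 evaluable and 128 recruited per arm (126 by normal approximation), not 120. The shortfall is about 5% to 6% in numbers and about 2 percentage points in power. A drop-out inflation by × 1.25 in place of / 0.75 is the likeliest cause, but this is an inference.

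The consequence for the trial is small. The target of 150 per arm exceeds the corrected requirement, so the error lies in the justification and not in the planned power.

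**What to change.** In Protocol section 4, item 14:

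1. Replace 120 with 128 per arm, state that alpha is two-sided 0.05, and show the steps: 64 × 1.5 = 96 evaluable, 96/0.75 = 128 recruited.
2. After the sentence that sets 150 per arm, add that this gives about 86% power at 25% loss (about 225 participants with follow-up data) and keeps 80% power up to about 36% loss.

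If the authors meant a one-sided test or a design effect that changes with cluster size, they should say so and show the calculation instead.

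The cost is a few sentences. The recruitment target of 300 and the number to be screened stay as they are.
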